### 9.2. Analysis Sets

For the purposes of analysis, the following analysis sets are defined:

| Participant Analysis Set | Description                                                                                                                                                                                                                                                                              |
|--------------------------|------------------------------------------------------------------------------------------------------------------------------------------------------------------------------------------------------------------------------------------------------------------------------------------|
| Full analysis set        | 
 
All participants having received at least one dose of study intervention and who have at least one efficacy evaluation after baseline. Participants will be included in the analyses according to the planned randomized intervention.
 
 |
| Safety analysis set      | 
 
All participants who are exposed to a study intervention. Participants will be analysed according to the intervention they actually received.
 
                                                                                          |

The full analysis set is used to analyse endpoints related to the efficacy objectives and the safety analysis set is used to analyse the endpoints and assessments related to safety.

The following data points sets are defined:

| Defined Data Points Sets | Description                                                                                               |
|--------------------------|-----------------------------------------------------------------------------------------------------------|
| DPS1                     | 
 
All observed data will be included in the analysis set.
 
 |

| Defined Data Points Sets | Description                                                                                                                                                                                                 |
|--------------------------|-------------------------------------------------------------------------------------------------------------------------------------------------------------------------------------------------------------|
| DPS2                     | 
 
For participants who discontinue study intervention and/or receive rescue therapy, post-discontinuation or post-rescue observations will not be included.
 
 |

Full analysis set and DPS1 are used to estimate the primary endpoints and the secondary endpoints for secondary core objective.

Full analysis set and DPS2 are used to for sensitivity analyses.

Safety analysis set and DPS1 are used to present safety data.

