## **6. Study Interventions and Concomitant Therapy**

Study intervention is defined as heterologous boosted strategy based on approved SARS-CoV-2 vaccine intended to be administered to a study participant according to this protocol.

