#### **6.1.2. Control arm:**

The control arm (Group 2) will have no vaccine administration. If primary analysis at 14 days confirms the starting hypothesis, subjects randomized to no vaccination will be considered for administration of one dose of COMINARTY at day 28th according to Public Health Department of the Ministry of Health recommendations on heterologous vaccination. If vaccinated, subjects will be followed at the time points defined in the flowchart (Group 2).

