### 9.3. Statistical Analyses

#### 9.3.1. General considerations

All analyses will be carried out using the statistical software SAS, version 9.4 of the SAS system for Windows.

All continuous variables will be summarized using the following descriptive statistics: n (non-missing sample size), mean, standard deviation (SD), 1st quartile, median, 3rd quartile, maximum and minimum. Absolute and relative frequencies (based on the non-missing sample size) of observed levels will be reported for all categorical variables.

All continuous variables will be tested for normality hypothesis assumption with the kolmogorov-Smirnov test. The antibodies binding to the SARS-CoV-2 S protein will be measured as lognormal distribution to obtain more nearly symmetric distribution.

The number of participants and the flowchart of the study will be presented. The period of enrolment and the total number of participants screened to be included in the study will be presented. The number of ineligible participants and the total number of randomized participants will be presented. The number of participants who never receive the study intervention will also be presented by treatment group and those who were included in the full analysis set and the safety analysis set will be presented.

Baseline is considered as the day 1 visit and the baseline data is data collected just before intervention at day 1. Participants with missing baseline value will be excluded from the analysis.

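### The full analysis set in Section 9.2 requires a dose of study intervention, so as worded it admits no control to the Day 14 primary analysis

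*Protocol*

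**What the plan says.** Protocol Section 9.2 makes membership of the full analysis set depend on dosing: "All participants having received at least one dose of study intervention and who have at least one efficacy evaluation after baseline". The next sentence places members in arms: "Participants will be included in the analyses according to the planned randomized intervention". The set then carries the main result: "Full analysis set and DPS1 are used to estimate the primary endpoints".

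Section 6 fixes what a dose would be: "Study intervention is defined as heterologous boosted strategy based on approved SARS-CoV-2 vaccine". Section 7.1 narrows this to one COMIRNATY injection at the randomisation visit. For the comparator, Section 6.1.2 says "The control arm (Group 2) will have no vaccine administration". A control may be offered COMIRNATY at Day 28 at the earliest, and only after the Day 14 analysis has confirmed the hypothesis.

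Two related rules sit nearby. The safety set is "All participants who are exposed to a study intervention". Section 9.3.1 adds, without limiting it to any one analysis: "Participants with missing baseline value will be excluded from the analysis".

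**The concern.** Section 9.1 defines G(Y2) in people who were not given COMIRNATY at randomisation, and Section 9.3.2 tests one arm against the other at Day 14. The population rule shuts out exactly the people whom the hypothesis needs. Neither set in Section 9.2 holds an unvaccinated control, and the sensitivity analyses on DPS2 start from the same full analysis set, so they do not cover the gap.

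Three further effects follow from tying membership to a dose:

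- At later visits a control would belong to the set only after crossing over, which is a post-randomisation event.
- In Group 1 the rule removes people who were randomised but not vaccinated. Section 8 lists the review of vaccination-cancellation criteria after randomisation, so such people can exist. If controls were restored and nothing else changed, this exclusion would act in one arm only.
- Serious adverse events are collected from randomisation in both arms, but those of unvaccinated controls belong to no analysis set.

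**Working it through.** **The plan's own figure.** Inputs from Section 9.5, case 2: CV 1.2, ratio 1.35, alpha 0.01, power 80%, allocation 2:1.

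- Log-scale SD = √ln(1 + 1.2²) = √ln 2.44 = 0.9445; ln 1.35 = 0.3001.
- n(control) = (1 + 1/2) × [SD × (z_alpha + z_0.80) / ln 1.35]².
- With z_alpha = 2.5758 (two-sided 0.01) and z_0.80 = 0.8416: 1.5 × (0.9445 × 3.4174 / 0.3001)² = 173.5. The table gives 173.506, and the formula matches all 12 rows.
- With z_alpha = 2.3263 (one-sided 0.01, as the text states): 1.5 × (0.9445 × 3.1679 / 0.3001)² = 149.1. That mismatch is a separate matter, and it errs on the safe side.
- Total: (173.506 + 347.012) × 1.15 = 598.6, close to the planned 600 (400 and 200).

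The design therefore needs about 174 evaluable controls by its table, or 150 by its stated one-sided test.

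**Counting members at Day 14.** This applies Section 9.2 to the arms in Sections 6 and 6.1.2.

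| Arm | Planned | Dosed by Day 14 | In the set as worded | In the set if no dose is required |
|---|---|---|---|---|
| Group 1 | 400 | up to 400 | up to 400 | up to 400 |
| Group 2 | 200 | 0 | 0 | up to 200 |

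The excluded share is 200/600 = 33%. The standard error of the log ratio is SD × √(1/n1 + 1/n2). With n2 = 0 it does not exist, so there is neither an estimate nor a test.

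**Later visits.** Group 2 membership would lie between 0 and 200, according to crossover and to having a post-baseline evaluation. A control given a second VAXZEVRIA dose, which Section 4.1 foresees, would stay outside, because that dose is not a heterologous boost.

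**Group 1.** The protocol gives no rate of randomised but undosed participants. Each percentage point is 0.01 × 400 = 4 people.

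**After correction.** For 400 and 200, the standard error is 0.9445 × √(1/400 + 1/200) = 0.0818. Power = Φ(0.3001/0.0818 − z_alpha), which is 91.0% one-sided or 86.3% two-sided at 0.01. With 15% non-evaluable (340 and 170) it is 85.5% or 79.0%. The correction calls for no change in sample size.

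**Baseline.** The t-test in Section 9.3.2 compares Day 14 log titres and uses no baseline value. The change-from-baseline comparisons in the synopsis do need one.

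**Safety data.** The Group 2 crossover flowchart in Section 1.2 marks serious and medically attended events from V1, but starts the solicited and unsolicited e-diary collection at Visit 4, with the boost.

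**The case against.** The best defence is that nobody could misread the intent. Section 9.1 names the unvaccinated group, Section 9.3.2 compares two arms, Section 9.5 plans 200 controls, and Section 9.2 itself sorts members by randomised arm. No analyst would run a one-arm primary analysis. This stands, and it limits the point to a faulty definition. It does not make the definition right. The sentence on randomised intervention assigns arms to people already admitted and does not lift the dose condition. Calling no vaccination an intervention does not help either, because the rule asks for a dose.

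Some stronger readings are tempting, and the protocol does not support them:

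- *Any repair would be a post-hoc change of population.* Restoring the controls is forced by Sections 9.1 and 9.3.2, and Section 9 says the SAP will be final before database lock. The choice left open is what to do with randomised but undosed Group 1 participants.
- *Safety lacks a concurrent comparator, and a new safety set would supply one.* Most safety endpoints are timed from vaccination, so a set of exposed participants suits them. In the crossover schedule, e-diary data for Group 2 start only at the boost, and no change to Section 9.2 can create earlier data. The valid remainder is the serious and medically attended events.
- *The missing-baseline rule biases the comparison or calls for imputation.* Section 8 lists the baseline blood draw ahead of randomisation, so in expectation the exclusion favours neither arm and mainly costs precision. Imputation would serve a covariate that the plan does not use.

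**Conclusion.** The point holds as an error of definition in the primary population. On the wording of Sections 6, 6.1.2 and 9.2, the Day 14 full analysis set contains 0 of 200 controls, and the primary ratio cannot be estimated. This rests on those definitions alone and on the planned 400 and 200; it does not depend on the variance or effect assumptions.

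A reader might infer that the trial stands to lose a third of its data or its power. The protocol does not support that, since both arms are plainly meant to be analysed. The practical exposure is smaller: an undocumented choice about undosed Group 1 participants in an open-label trial, later-visit membership that depends on crossover, and control-arm serious and medically attended events without an analysis set. The number of undosed participants is not stated, so the size of that part is unknown. The baseline exclusion is a minor addition.

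**What to change.** In Section 9.2, define the full analysis set as all randomised participants with at least one post-baseline immunogenicity result, analysed in the arm to which they were randomised, whether or not a dose was given.

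In Section 9.3.1, limit the exclusion for a missing baseline value to the change-from-baseline analyses.

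For events collected in both arms from randomisation (serious events, and medically attended events as the Group 2 flowchart marks them at V1), let the safety set include Group 2. Count these participants as unvaccinated until any vaccine dose and as COMIRNATY after crossover. State that solicited and unsolicited e-diary events remain summaries after vaccination, without a concurrent control.

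The cost is a few lines in Sections 9.2 and 9.3.1, carried into the SAP. Sample size, visits and data collection do not change.

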### 9.3. Statistical Analyses

#### 9.3.1. General considerations

All analyses will be carried out using the statistical software SAS, version 9.4 of the SAS system for Windows.

All continuous variables will be summarized using the following descriptive statistics: n (non-missing sample size), mean, standard deviation (SD), 1st quartile, median, 3rd quartile, maximum and minimum. Absolute and relative frequencies (based on the non-missing sample size) of observed levels will be reported for all categorical variables.

All continuous variables will be tested for normality hypothesis assumption with the kolmogorov-Smirnov test. The antibodies binding to the SARS-CoV-2 S protein will be measured as lognormal distribution to obtain more nearly symmetric distribution.

The number of participants and the flowchart of the study will be presented. The period of enrolment and the total number of participants screened to be included in the study will be presented. The number of ineligible participants and the total number of randomized participants will be presented. The number of participants who never receive the study intervention will also be presented by treatment group and those who were included in the full analysis set and the safety analysis set will be presented.

Baseline is considered as the day 1 visit and the baseline data is data collected just before intervention at day 1. Participants with missing baseline value will be excluded from the analysis.

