## 1.2. Flowchart.

### Group 1

| Visit number                                                                                |                                      | V1                      | V2        | V3         | V4         | V5          | V6           | V7           |
|---------------------------------------------------------------------------------------------|--------------------------------------|-------------------------|-----------|------------|------------|-------------|--------------|--------------|
| Procedure                                                                                   | Screening                            | Randomization/
Boost | Visit 2   | Visit 3    | Visit 4    | Visit 5     | Visit 6      | End of study |
| Day $\pm$ window                                                                            | 0 to 7 days before boost vaccination | 0                       | 7 $\pm$ 2 | 14 $\pm$ 3 | 28 $\pm$ 3 | 90 $\pm$ 10 | 180 $\pm$ 10 | 360 $\pm$ 14 |
| Screening for eligibility                                                            |                                      |                         |           |            |            |             |              |              |
| Eligibility check                                                                           | X                                    |                         |           |            |            |             |              |              |
| Informed consent                                                                            | X                                    |                         |           |            |            |             |              |              |
| PCR                                                                                         |                                      | X                       |           |            |            |             |              |              |
| Baseline procedures                                                                  |                                      |                         |           |            |            |             |              |              |
| Randomization                                                                               |                                      | X                       |           |            |            |             |              |              |

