| Solicited local and systemic adverse events (AEs) for 7 days after vaccine . Via E-diary    |                                      | X                       |           |            |            |             |              |              |
| Unsolicited local and systemic adverse events (AEs) for 28 days after vaccine . Via E-diary |                                      | X           |           |            |            |             |              |              |
| Unsolicited SAEs                                                                            |                                      | X                       |           |            |            |             |              |              |
| Medically-attended adverse events (MAAEs)                                                   |                                      | X                       |           |            |            |             |              |              |
| Immune response evaluation                                                                  |                                      | X                       | X         | X          | X          | X           | X            | X            |

1. Temperature, blood pressure and heart rate

2. Lab determination could be performed either at screening visit or randomization3. Two days per week

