### **Visit 1. Randomization**

- PCR
- Review medical history
- Review medication history
- Measure vital signs (body temperature, pulse, blood pressure).
- Blood extraction for immune response evaluation.
- Blood extraction for lab safety determinations.
- Randomization.
- Pregnancy test

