#### 9.3.2. Primary endpoint(s) analysis

The immune response measured by immunoassay 14 days after randomisation between the two arms will be tested by one-tailed t-test assuming symmetric distribution of lognormal transformation. Geometric means will be calculated as the mean of the assay results after making the logarithm transformation and then exponentiating the mean to express results on the original scale. One-sided 95% CIs will be obtained by taking natural log transforms of concentrations/titers, calculating the 95% CI with reference to the t-distribution, and then exponentiating the confidence limits. In other case, Mann-Whitney-Wilcoxon test will be used.

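### Section 9.3.1 excludes anyone with a missing baseline value without limit, although the primary test uses no baseline, and its baseline definition does not accept the screening laboratory panel that the flowcharts allow

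*Protocol*

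**What the plan says.** Section 9.3.1 (General considerations) sets two rules for all analyses, one defining baseline and one dealing with its absence. It takes the Day 1 visit as baseline and continues: "baseline data is data collected just before intervention at day 1. Participants with missing baseline value will be excluded from the analysis". The second rule is not tied to a particular variable or analysis.

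Three other places bear on these rules.

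- **Section 9.2** defines data point set DPS1 as everything observed, and pairs it with the full analysis set for the primary endpoint.
- **Section 9.3.2** compares the two arms on the Day 14 immunoassay result, which "will be tested by one-tailed t-test assuming symmetric distribution of lognormal transformation". No baseline covariate or change score enters.
- **Section 1.2** carries the same footnote under the Group 1 and Group 2 flowcharts: "Lab determination could be performed either at screening visit or randomization". The screening column is headed "0 to 7 days before boost vaccination". The Visit 1 list in section 8 includes "Blood extraction for lab safety determinations" and does not mention the screening alternative.

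**The concern.** A rule placed under general considerations governs the primary analysis unless something limits it, and nothing does. A participant who was randomised and has a Day 14 titre but no Visit 1 titre is included by section 9.2 and excluded by section 9.3.1. Two analysts following the protocol could therefore report different primary populations. The exclusion gains nothing, because the test does not use the value whose absence triggers it.

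The definition of baseline raises a second problem. A site that draws the safety panel at screening follows the flowchart, yet its panel was not collected at the Day 1 visit just before intervention. If a laboratory summary is referenced to baseline, that participant counts as missing and the exclusion applies. Abnormal laboratory values at the 1-month visit are among the primary safety endpoints, so the denominator of such a summary matters.

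For controls who cross over, the same definition fixes the laboratory reference at randomization, about four weeks before their dose.

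**Working it through.** **1. The rules side by side, for a randomised participant with a Day 14 titre and no Visit 1 titre**

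| Source | Treatment of this participant |
|---|---|
| Section 9.2, DPS1 | Day 14 titre is observed, so it is used |
| Section 9.3.2 | Day 14 log titre is the only value the test needs |
| Section 9.3.1 | Baseline value is missing, so the participant is excluded |

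The first two agree with each other and conflict with the third.

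**2. Reproducing the plan's sample size (section 9.5)**

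Inputs: ratio 1.35, coefficient of variation (CV) 1.2, 80% power, alpha 0.01, 2:1 allocation, 400 + 200 = 600.

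- Log-scale SD = sqrt(ln(1 + 1.2²)) = sqrt(ln 2.44) = 0.944.
- Log effect = ln 1.35 = 0.300.
- n(control) = (1 + 1/2) × [SD × (z_alpha + z_beta) / ln 1.35]².
- With z_alpha = 2.576 and z_beta = 0.842, this gives 173.506, the tabulated figure. The COMIRNATY arm is twice that, 347.012, and the total is 520.5.
- 520.5 × 1.15 = 599, which matches the planned 600.

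The table reproduces with the two-sided 0.01 critical value. The one-sided 0.01 level named in the text (z_alpha = 2.326) gives 149.098. This difference is a separate matter, but it means that power is best shown at both critical values.

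**3. What the exclusion would cost the primary test**

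The protocol gives no rate of missing Visit 1 titres, so the loss L is an assumption and is applied equally to both arms.

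- SE = 0.944 × sqrt(1/(400(1−L)) + 1/(200(1−L))).
- Power = Φ(0.300/SE − z_alpha).

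| Loss L | Participants discarded | SE | Power, one-sided 0.01 | Power, two-sided 0.01 critical value |
|---|---|---|---|---|
| 0 | 0 | 0.0818 | 91.0% | 86.3% |
| 1% | 6 | 0.0822 | 90.7% | 85.9% |
| 5% | 30 | 0.0839 | 89.4% | 84.1% |
| 15% | 90 | 0.0887 | 85.5% | 79.0% |

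Confidence intervals widen by 1/sqrt(1−L): 0.5% at L = 1% and 2.6% at L = 5%. The 15% row equals the whole non-evaluable allowance and serves as an outer bound. Exclusions under this rule would come on top of any other loss.

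**4. The laboratory baseline**

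- Permitted draw: screening, up to 7 days before randomization, or Visit 1 (both flowcharts).
- Accepted by section 9.3.1: the Day 1 visit only, just before intervention.
- A compliant screening-only panel therefore leaves no laboratory baseline.

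For a crossed-over control, the Group 2 flowchart schedules panels at Visit 4 (Day 28 ± 3, the dosing visit) and Visit 5. Section 8 lists the Visit 4 laboratory determination ahead of the control-arm vaccination steps. Under section 9.3.1 the Visit 4 panel could not serve as the reference. The reference would instead be a panel taken 25 to 31 days before the dose.

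No share of screening-only panels is given, and no baseline-referenced laboratory analysis is described. The number affected cannot be estimated from the protocol.

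**The case against.** The strongest reply is that the exclusion sentence is loose rather than wrong. It can be read as applying only to an analysis that needs the missing value, and DPS1 supports that reading for the primary endpoint. The Visit 1 list also places the immune sample ahead of randomization. Excluding people on a value taken before randomization does not by itself unbalance the arms, so the cost is precision, and step 3 shows that this cost is small. These arguments limit the size of the problem. They do not remove the contradiction, because the sentence carries no such limit and stands where it applies to everything.

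On laboratory data, the reply is that the endpoint is an abnormality at a post-dose visit and not a change from baseline, that section 9.3.5 describes no baseline-referenced laboratory analysis, and that section 8 lists a laboratory draw at Visit 1. This stands, so the laboratory part is conditional on such a summary being produced.

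A reader might infer three stronger points, and the documents do not support them.

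- **That controls drop out because they have no Day 1 intervention.** Section 8 lists "Blood extraction for immune response evaluation" at Visit 1, separately from the vaccination-arm steps. Both flowcharts show the sample at Visit 1, and the synopsis names the randomization visit as baseline for both groups. Day 0 in the flowcharts and Day 1 in section 9.3.1 are labels for the same visit. The full analysis set's requirement of at least one dose does literally exclude undosed controls, but that is a separate problem.
- **That a screening-only laboratory panel removes a participant from the primary titre comparison.** The sentence does not name the variable, but nothing links a laboratory baseline to the titre analysis.
- **That large numbers are lost from laboratory safety.** No share of screening panels is given. The safety set holds only exposed participants, initially about 400 and not 600.

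**Conclusion.** The point holds in a limited form. Section 9.3.1 states an unrestricted exclusion that conflicts with DPS1 in section 9.2 and serves no purpose in the unadjusted Day 14 test of section 9.3.2. Followed literally, it discards randomised participants who have a usable primary endpoint.

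The consequence is a departure from the randomised population and a modest loss of precision. On an assumed 1% to 5% of missing Visit 1 titres, equal in both arms and with CV 1.2 and ratio 1.35, power falls by 0.3 to 1.6 percentage points at the stated one-sided 0.01 level. At the critical value that reproduces the sample size table, it falls by 0.4 to 2.2 points. The trial's ability to answer its primary question is not at risk from this sentence.

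The definition of baseline also conflicts with the laboratory schedule in both flowcharts. That would matter for any baseline-referenced laboratory summary, but its extent cannot be determined from the protocol.

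**What to change.** Amend section 9.3.1 in two respects.

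1. **Exclusion.** Keep every randomised participant with a Day 14 titre in the primary analysis. Restrict the missing-baseline exclusion to change-from-baseline summaries of the variable concerned.
2. **Definition.** Define baseline as the last non-missing value before vaccination in Group 1, and on or before randomization in Group 2, accepting laboratory panels drawn at screening. For post-dose laboratory summaries in crossed-over controls, use the last value before their dose.

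The Group 1 wording keeps a sample drawn after randomization but before the dose on the same day, as the present text does. The full analysis set's dosing requirement in section 9.2 should be reconciled at the same time, since otherwise the first change would not reach undosed controls.

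The cost is a few sentences and no new data. The drawback is that some laboratory baselines may be up to 7 days older than the randomization visit.
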